### Economic analysis plan

This will be performed from the perspective of the healthcare provider (i.e. HMC). The benefit-to-cost ratio (sum of cost savings and cost avoidance)/ (operational cost of the deprescribing plan), and the net benefit (sum of cost savings and cost avoidance) – (operational cost of the deprescribing plan) will be calculated.
The total economic benefit of the deprescribing intervention will be calculated as the sum of the cost-savings resulting from medications use, and the cost avoidance associated with the intervention programme compared to usual care. Cost-savings based on the intervention will be the reduced cost of therapy associated with the reduction in utilisation (DDDs) of the targeted drugs, compared to the usual care. Cost avoidance will be the cost avoided by reducing ED visits and hospitalisations as unintended consequences of the polypharmacy use of medications.The cost of the programme will be represented by the operational cost of running the deprescribing intervention plan. The costs will include commonly considered non-protocol-driven resources that are strictly utilised under the different stages of the intervention plan workflow, including development and implementation. Also, the cost of the programme is any increase in the cost of medication use, hospitalisation, and ED visits, if any, compared to the usual care. Only direct medical costs will be considered in calculating the monetary value of the benefit associated with drug use, hospitalisation, and emergency admissions.

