### Deprescribing intervention and workflow

The proposed deprescribing workflow consists of the following stages:
Patient assessment: Upon recruitment, the patient’s information is collected through participant interviews and electronic medical records (via Cerner). These include sociodemographic, clinical, and medication information. Additionally, patients complete self-reported questionnaires to assess medication adherence, treatment burden, and quality of life.Deprescribing plan development: For patients in the intervention group, the clinical pharmacist highlights the potentially problematic medications, drafts a deprescribing plan for each, consult the multidisciplinary team and the relevant specialists, and documents in the patient’s medical records. The potentially problematic medications are identified through the Medication Appropriateness Index (MAI) tool, and the deprescribing plans are drafted using deprescribing algorithms adapted from evidence-based deprescribing guidelines in the CKD setting (Zidan et al., 2025). Validation of these algorithms was conducted through input from an expert panel and piloted during the pilot RCT. The results of the validation and piloting are not yet published. The intervention targets all PIMs as we intend to provide a holistic approach. Prioritising the deprescribing plans is based on patient safety and medication properties. Only one medication is targeted per deprescribing cycle, unless deemed clinically appropriate. These are decided on case-by-case basis during the MDT-CKD meetings.Implementation and monitoring of the deprescribing intervention: The team implements and monitors the approved deprescribing plan during the patient’s appointments at the centre or through follow-up phone calls, as applicable. The team periodically reviews the intervention’s progress, discussing results and addressing any issues to take corrective actions. Monitoring protocols are tailored per medication class as per the clinical guidelines.Deprescribing plan finalisation: During subsequent appointments, the medication plan is reconciled and discussed with the patient. Patients are provided with a deprescribing card, containing updated medication information to ensure clear communication and adherence to the revised regimen.Post-deprescribing follow-up: For each deprescribing plan, the MDT-CKD clinical pharmacist conducts three follow-up interviews or phone calls with the patients on days 2, 7, and 28 post-deprescribing. These follow-ups are designed to monitor late-onset withdrawal symptoms and to address any questions or concerns raised by the patient. Any changes to the patient’s medication regimen are documented and discussed with the multidisciplinary team to ensure appropriate management.Documentation: All deprescribing processes and decisions related to each medication are documented in the participant’s medical records. For process evaluation, a checklist detailing each step of the deprescribing process is completed for every participant to ensure the fidelity of the intervention.

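### The cost–benefit formulas leave out cost increases that the same section counts as programme cost, and drug savings and drug increases are measured on different sets of drugs

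*Protocol article*

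**What the plan says.** All the relevant definitions stand in the Economic analysis plan of the Protocol article.

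- Ratio: "The benefit-to-cost ratio (sum of cost savings and cost avoidance)/ (operational cost of the deprescribing plan". Operational cost is the only denominator.
- Net benefit: "the net benefit (sum of cost savings and cost avoidance) – (operational cost of the deprescribing plan) will be calculated". Operational cost is again the only amount subtracted.
- Programme cost, first statement: "The cost of the programme will be represented by the operational cost of running the deprescribing intervention plan".
- Programme cost, second statement: "Also, the cost of the programme is any increase in the cost of medication use, hospitalisation, and ED visits, if any", again relative to usual care.
- Total benefit in general terms: "the sum of the cost-savings resulting from medications use, and the cost avoidance associated with the intervention programme compared to usual care".
- The drug part of that benefit in detail: "Cost-savings based on the intervention will be the reduced cost of therapy associated with the reduction in utilisation (DDDs) of the targeted drugs", again relative to usual care.

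Two other sections bear on the phrase about targeted drugs. Under Deprescribing intervention and workflow, the pharmacist flags problematic medications and drafts plans for intervention patients, and "The intervention targets all PIMs as we intend to provide a holistic approach". Under Secondary outcomes, the deprescribing outcome counts substituted and restarted drugs as well as stopped and reduced ones, grouped by targeted drug class.

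**The concern.** Cost–benefit is part of the stated aim of the trial and a listed secondary outcome, so its two summary measures should each have one definition. Two features prevent that.

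First, the second statement of programme cost introduces an amount for which neither formula has a place. An analyst who follows the formulas ignores it; an analyst who follows the later sentence charges it. The same data then give different answers, and the version that ignores increases always looks better for the programme.

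Second, decreases in drug cost are defined on the targeted drugs, while increases are defined on medication use generally. Replacing one drug by another is part of the intervention, so a fall in a targeted drug may be offset, wholly or partly, by a rise in a drug outside that set. In addition, individual plans are drafted only in the intervention arm, and the section does not say which drugs in a control patient form the comparison. Both gaps can credit the programme with savings that it did not produce.

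**Working it through.** The article gives no unit costs, savings, ratio or net benefit, so there is no stated figure to reproduce. All cost amounts below are assumptions in arbitrary units.

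**Step 1: the cost term.** Let B = drug savings plus cost avoidance, O = operational cost, and I = increases in medication, hospitalisation and ED cost relative to usual care.

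- As printed: ratio = B/O; net benefit = B − O.
- With the later sentence: ratio = B/(O + I); net benefit = B − O − I.

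The printed ratio is too high by the factor (O + I)/O = 1 + I/O, and the printed net benefit by I.

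| B | O | I | Ratio, printed | Ratio, later sentence | Net benefit, printed | Net benefit, later sentence |
|---|---|---|---|---|---|---|
| 200 | 50 | 50 | 200/50 = 4.0 | 200/100 = 2.0 | 150 | 100 |
| 200 | 100 | 0 | 2.00 | 2.00 | 100 | 100 |
| 200 | 100 | 10 | 2.00 | 200/110 = 1.82 | 100 | 90 |
| 200 | 100 | 50 | 2.00 | 200/150 = 1.33 | 100 | 50 |

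The two readings agree only when I = 0.

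**Step 2: the scope of drug costs.** Suppose that targeted drugs fall by 200 relative to usual care and that other drugs, including substitutes, rise. Read the increase sentence as applying to total medication cost.

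- Other drugs rise by 80. Total drug cost changes by −200 + 80 = −120, which is not an increase, so nothing is charged. The plan credits 200; the actual saving is 120.
- Other drugs rise by 250. Total drug cost changes by −200 + 250 = +50, so 50 is charged. The plan shows 200 − 50 = 150 before operational cost; the actual result is −50.

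If the increase sentence is instead applied drug by drug, the whole 80 or 250 is charged, and the result before operational cost is right (120 or −50). The text does not say which reading is meant.

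**Step 3: the control-arm list.** A simulation with no intervention effect used 125 patients per arm (the planned number) and 2,000 runs. It assumed 10 drugs per patient, 20% of them potentially inappropriate medications (PIMs), and the same natural stopping rate in both arms. If controls have no list, the expected spurious saving is 10 × 0.20 × stopping rate.

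| Stopping rate | Expected, no control list | Simulated, no control list | Simulated, same PIM definition in both arms | Simulated, all drugs in both arms |
|---|---|---|---|---|
| 5% | 0.10 | 0.101 | 0.001 | 0.005 |
| 10% | 0.20 | 0.202 | 0.003 | 0.001 |
| 20% | 0.40 | 0.400 | 0.002 | 0.004 |

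Entries are stopped drugs per patient, not costs. The spurious saving appears only when controls have no counterpart list; with an identical definition it is about zero.

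**The case against.** The best defence is to read the section as a whole. The later sentence then completes the definition of programme cost, and the plan yields one ratio (2.0 in the first example) and one net benefit (100). That reading is reasonable, but both formulas are printed in full with operational cost alone, and a reader who applies them gets 4.0 and 150. The sensitivity analyses vary the base-case inputs; they do not settle which formula applies.

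A reader might infer that targeted drugs exist only in the intervention arm and that the saving is therefore biased. The documents do not support so firm a statement. Savings are defined relative to usual care, the intervention is said to target all PIMs, PIMs are assessed by the same tool in both groups, and the secondary outcomes speak of targeted drug classes. A matching control list can be built from any of these. What stands is that the section does not name one.

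A reader might also infer that the plan offers a third ratio, with increases netted from the benefit: (200 − 50)/50 = 3.0. The document contains no such rule. The later sentence is in fact the stricter of the two: B/(O + I) is below (B − I)/O whenever B exceeds O + I. Both equal 1 at B = O + I, so they agree on whether the programme pays for itself, and net benefit is the same under either.

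Nor are substitute costs plainly ignored, since the general description of benefit covers medication use and the increase sentence could be applied drug by drug. That defence depends on a reading that the text does not fix.

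Finally, this is a secondary outcome, and a journal article may leave costing detail to a fuller document. That would excuse an omission, but not two printed statements that conflict.

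**Conclusion.** The contradiction in the cost term is established from the text. Its effect is exact in form: the printed ratio is overstated by the factor 1 + I/O and the printed net benefit by I, with no effect if no cost rises. With assumed amounts of 200, 50 and 50, the ratio is 4.0 rather than 2.0 and net benefit 150 rather than 100.

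The mismatch in scope is also in the text, but overstatement from it is conditional. It arises if substitute costs are not netted (200 credited against 120 in the example) or if controls have no matching list (0.10 to 0.40 spurious stopped drugs per patient under the assumed turnover). It does not arise from the list if PIMs or classes are defined identically in both arms. All amounts are illustrative, because the article gives no costs.

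The point should be corrected, but it touches only the economic outcome. Whether the ratio or the net benefit is presented first is a matter of preference and not part of the finding.

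**What to change.** For every randomised patient, total the cost of all medications (substitutes included), all hospitalisations and all ED visits from randomisation to 6 months. Define the benefit as the signed difference, control minus intervention, adjusted for baseline. Keep only operational cost in the cost term of both formulas, and delete the sentence that adds increases to programme cost. Report targeted drug classes descriptively.

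Rises and falls then enter in the same place whatever the result. In the first example the benefit is 200 − 50 = 150, the ratio 150/50 = 3.0 and the net benefit 150 − 50 = 100. In the two drug examples the drug component is 120 and −50. Because this ratio is higher than the 2.0 given by the later sentence, the rule should be fixed in writing before costs by arm are seen.

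Merely adding the increase to the cost term of both printed formulas would end the contradiction, but would leave the mismatch between targeted drugs and all medication use.

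The cost is a change of wording and the pricing of all drugs. Prescription information, hospitalisations and ED visits are already collected. The downside is more pricing work and probably a smaller stated saving.

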#### Sensitivity analysis

Sensitivity analysis will be used to enhance the robustness of the economic study conclusion and to enhance the generalizability of the study findings. The analysis tests will be used to assess modification on the base-case values of variables in relation to the costs and clinical probabilities. One-way and multivariate sensitivity analysis will be undertaken to analyze the effect of uncertain variables on the study conclusions. Both probabilistic analyses will be conducted via Monte Carlo simulation, [contact] (Palisade Corporation, NY).

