#### Secondary outcomes

***Pill burden:***Frequency and total number of daily medications, collected from medical records and confirmed during patient interviews. Pill burden was operationalised as a simple count of medications combined with their frequency of administration per day. This measure did not account for dosage forms or specific administration instructions.***Deprescribing outcome:*** Total medications successfully discontinued, dose-reduced, substituted, or restarted after intervention (at 6-month follow-up), categorised by targeted pharmacological drug class.***Health-related quality of life (HRQoL)****:* This will be measured using the self-administered Kidney Disease Quality of Life (KDQOL™) questionnaire (Hays et al., 1994).***Treatment burden:*** This will be assessed using the Treatment Burden Questionnaire (TBQ) (Tran et al., 2014).***Medication adherence****:* Assessed using the Adherence to Refills and Medications Scale (ARMS), a validated self-administered adherence measuring tool (Kripalani et al., 2009). Both English and Arabic versions of the tool are available for use in patients with chronic diseases (Alammari et al., 2021; Kripalani et al., 2009; Zidan et al., 2018).***Hospitalizations and emergency department (ED) visits:*** Total number of hospitalisations and ED visits six months after the intervention. This will be extracted from medical records (CERNER).***Cost–benefit and cost-savings:*** The return on investment in the proposed deprescribing intervention will be measured through cost–benefit analysis, considering cost-savings from drug use, hospitalisations, and ED visits compared to intervention costs.***Unanticipated adverse events:*** Withdrawal symptoms (e.g. dyspepsia after stopping PPIs) or the need for drug re-initiation may be encountered in some cases. Each class of medications has different expected withdrawal symptoms. These or any other unanticipated events will be documented and reported to MRC-IRB as per IRB SOP-09.

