#### Detailed analyses approach

For all analyses, differences between treatment groups will be reported with 95% confidence intervals, and statistical significance will be assessed at the two-sided 0.05 level.
Analysis of PIMs (primary outcome) between groups at 6 months will be performed using Poisson regression with adjustment of baseline values, age, comorbidities, and dialysis group. Secondary outcomes will be analyzed similarly, using either ordinary least squares or Poisson regression, as appropriate.Outcomes with repeated measures at 3 and 6 months, including the primary outcome, will be analyzed using mixed-effects models to account for correlated measurements within individuals over time. To assess differences between the two treatment groups, general linear models will include fixed effects for the treatment group, time point, and the interaction between the treatment group and the time point. Treatment effects will be reported separately at 6 months post-randomisation, regardless of the significance of the interaction term.For continuous outcomes, linear regression adjusted for baseline will be used without data transformations. Estimates of the treatment effect will be reported as mean differences in the change from baseline to 6 months between the intervention and control groups. For ordinal categorical outcomes, treatment effect estimates will be reported as proportional odds ratios for the intervention group compared with the control group using logistic regression. For nominal categorial (i.e. count) outcomes, treatment effects will be reported as rate ratios for the intervention group compared with the control group.Efforts will be made to minimise missing data. In case of encountering expected missing data, these will be documented and the reasons for missingness will be explored to enable the researchers to determine the proper imputation mechanism to estimate the missing values.

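### The economic plan states no interval for net benefit or the benefit-to-cost ratio that reflects the trial's own sampling error, although the resource-use data are held per patient

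*Protocol article*

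**What the plan says.** Economic analysis plan: "The benefit-to-cost ratio (sum of cost savings and cost avoidance)/ (operational cost of the deprescribing plan), and the net benefit" are to be calculated, and no interval is mentioned. The benefit side is drug savings plus avoided events: "Cost avoidance will be the cost avoided by reducing ED visits and hospitalisations". The same section later adds to programme cost any rise in drug, admission or ED cost over usual care, and it counts the development stage of the intervention as a cost.

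Sensitivity analysis, under the economic plan: "The analysis tests will be used to assess modification on the base-case values of variables in relation to the costs and clinical probabilities". Then: "One-way and multivariate sensitivity analysis will be undertaken to analyze the effect of uncertain variables on the study conclusions", and "Both probabilistic analyses will be conducted via Monte Carlo simulation". No ranges, distributions or sources for the inputs are given.

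The data are individual. Secondary outcomes lists "Total number of hospitalisations and ED visits six months after the intervention. This will be extracted from medical records (CERNER"), and the data collection form holds prescription information. The Statistical analysis plan section looks at the mean, SD, minimum and maximum of costs ahead of a statistical comparison, and names the t-test and the Mann-Whitney test. Detailed analyses approach promises, for all analyses, that "differences between treatment groups will be reported with 95% confidence intervals".

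**The concern.** Base-case values and clinical probabilities belong to decision models. The Economic analysis plan describes no such model. It describes differences between randomised arms in drug use, ED visits and admissions. The uncertain quantity is therefore the between-arm difference itself, and its uncertainty comes from which patients happened to be in each arm. Admissions are typically skewed and concentrated in a few patients, and someone who is admitted often also tends to have more ED visits.

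Varying base-case inputs around the observed values answers another question: how the result moves if prices or assumed effects differ. If that is the only uncertainty shown, a favourable chance difference in admissions becomes the base case and the variation is drawn around it. Economic benefit is one of the trial's two headline aims, so a ratio above 1 described as robust would carry weight.

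**Working it through.** **What an interval for net benefit needs.** Write net benefit as D + H + E − C, where D, H and E are the between-arm differences in drug, admission and ED cost and C is operational cost. With C fixed,

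Var(net benefit) = Var(D) + Var(H) + Var(E) + 2[Cov(D,H) + Cov(D,E) + Cov(H,E)].

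Confidence intervals for the components give the three variances but not the covariances. The Mann-Whitney test does not compare mean cost, which net benefit requires. So the intervals promised elsewhere do not add up to an interval for net benefit or the ratio.

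**Size.** The plan gives no figure for economic uncertainty to reproduce. It supplies only the arm size: 125 per group less 10% dropout is 112.5, taken as 112. Everything else below is assumed.

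*Mean cost.* The 95% half-width of a difference in mean cost, as a share of the usual-care mean, is 1.96 × CV × √(2/n), where CV is the coefficient of variation. With n = 112, CV 1 gives 26.2%, CV 2 gives 52.4% and CV 3 gives 78.6%.

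*Admissions only.* Assume negative binomial admissions with mean m over six months and gamma shape k, and a cost per admission with mean 1 and CV 1. The variance per patient is V(m) = 2m + m²/k. The expected saving is r·m, with SE = √{[V(m) + V((1−r)m)]/112}. Take m = 1, k = 1, r = 20%:
- V(1) = 3 and V(0.8) = 1.6 + 0.64 = 2.24
- SE = √(5.24/112) = 0.216
- 0.20 ± 1.96 × 0.216 is −1.1 to 3.1 times the expected saving
- P(wrong sign) = Φ(−0.20/0.216) = 18%

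Simulating the same model over m = 0.3 to 1.0 and k = 0.5 to 1.0 gives these 95% sampling ranges, as multiples of the expected saving:

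| True reduction | m = 1.0, k = 1 | m = 0.3, k = 0.5 | Wrong sign, all settings |
|---|---|---|---|
| 10% | −3.34 to 5.41 | −6.43 to 8.29 | 33% to 41% |
| 20% | −1.05 to 3.14 | −2.64 to 4.56 | 18% to 31% |
| 30% | −0.35 to 2.41 | −1.27 to 3.39 | 8% to 20% |
| 50% | 0.25 to 1.79 | −0.25 to 2.34 | 0% to 6% |

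*Input variation, for comparison.* Varying unit cost and effect uniformly and independently gives 0.65 to 1.42 times the base case at ±25% each, and 0.37 to 1.92 times at ±50% each. The sign cannot change, because the smallest product is 0.5 × 0.5 = 0.25.

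*Admissions and ED visits together.* Assume a shared patient frailty with variance v, an ED visit costing 15% of an admission, means a and e, and a true 15% reduction. The variance per patient is a + 0.15²e + v(a + 0.15e)². Take a = 0.5, e = 0.8, v = 1:
- usual care: 0.5 + 0.018 + 0.384 = 0.902
- intervention (a = 0.425, e = 0.68): 0.425 + 0.015 + 0.278 = 0.718
- SE = √(1.620/112) = 0.120; expected saving = 0.15 × 0.62 = 0.093
- half-width = 1.96 × 0.120/0.093 = 2.5 times the expected saving; wrong sign Φ(−0.093/0.120) = 22%

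Over a = 0.5 to 0.8, e = 0.8 to 1.2 and v = 1 to 2, the half-width is about 2.2 to 3.0 times the expected saving, and the sign is wrong in roughly 19% to 25% of trials. Drawing admissions and ED visits independently understates the SD by 7% to 11%.

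**Ratio against net benefit when a difference reverses.** Let S be drug savings and suppose event costs rise by R. With operational cost alone in the denominator the ratio is (S − R)/C. If the rise is moved to programme cost, it is S/(C + R). Both exceed 1 exactly when S > C + R, but otherwise they differ in value. Net benefit is S − R − C either way.

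**The case against.** The strongest defence has three parts. First, a condensed article may leave input distributions and interval methods to the full plan, and nothing says that the Monte Carlo step is the sole source of uncertainty. Second, sampling error is addressed elsewhere: a cost comparison is planned and group differences get 95% confidence intervals, so a noisy admission difference would be visible in the same report. Third, Monte Carlo can carry sampling error if its distributions are fitted to the trial's own estimates, standard errors and correlations.

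Much of this stands. A reader might infer that sampling error will go unmeasured, or that it dominates the economic result. The documents do not support either: component intervals are promised, fitted distributions are not excluded, and no event rate, cost spread or input range is given. A reader might also infer that the planned interval will be too narrow by a fixed multiple. On the admissions model at a 20% reduction with m = 1.0 and k = 1, the half-widths are (3.14 + 1.05)/2 = 2.10 for sampling and (1.92 − 0.37)/2 = 0.78 for ±50% input variation, a factor of about 2.7. At a 50% reduction the sampling half-width is (1.79 − 0.25)/2 = 0.77, and the factor is about 1. There is no single multiple. These models also leave out drug savings and operational cost, so they describe avoided event cost and not net benefit itself.

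The defence does not remove the core point. The article does choose and state a method for these two end points. That method is not said to rest on the trial's standard errors or on joint draws, and component intervals cannot be combined without covariances.

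**Conclusion.** The point holds as one about the stated method. The only uncertainty analysis tied to net benefit and the ratio varies base-case inputs. It is not said to carry the trial's sampling error or the within-patient correlation of costs, and no interval elsewhere clearly reaches these two quantities. An apparently robust ratio above 1 could coexist with data compatible with a loss.

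The size is illustrative. With 112 per arm, the assumed event rates and dispersion, and a true reduction of 15% to 20%, avoided event cost has the wrong sign in roughly 18% to 31% of trials. At about 50% the risk falls to 0% to 6%, and in the most favourable setting sampling error and ±50% input variation are similar in width. The point concerns a secondary, economic conclusion and leaves the primary outcome untouched. It should be settled before the economic data are analysed.

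**What to change.** Amend the Sensitivity analysis section as follows:

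- Resample patients with replacement within arm and dialysis stratum (for example 5,000 times). In each resample, recompute the between-arm differences in drug, admission and ED cost together, so that skewness and within-patient correlation are kept.
- Make net benefit the main economic estimate. Report its 95% bootstrap interval and the probability that it exceeds zero.
- Compute the ratio in each resample with operational cost alone as the denominator, and count cost increases as negative benefit. The definition then does not switch when a difference reverses. Align the Economic analysis plan sentence that moves such increases into programme cost.
- Hold programme costs that are not patient-level, such as development, fixed in the bootstrap. Keep one-way and Monte Carlo variation for those costs, unit prices and staff-time rates.

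The cost is a change of wording and slightly more analysis on data already being collected; trial conduct does not change. The reported economic interval will be wider.
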